#### Exclusion criteria

people who do not poses a telephone contact number; those with serious psychiatric problems; those with physical or psychiatric disabilities that impede their participation in the study; those with a terminal illness.

All centres of Barcelona province and the metropolitan area will be invited to participate, and those who voluntarily accept to participate will be included in the study. *To date, at the end of the recruitment period, 25 practices will participate in the study*.

### Data collection

In the inclusion visit, the health professional will gather the relevant medical data and history (illnesses, medication, alcohol consumption and psychoactive substances) from the patient's clinical record, after checking and completing it together with the patient. Then, relevant data on behaviour and risk-perception of suffering from an RTI, and data on previous traffic accidents will be collected.

A yearly follow up via telephone is expected to be performed.

### Study variables

#### We dispose of two data collection instruments in order to carry out this study

-A survey, which will be carried out by health professionals in a face to face interview. Data will be obtained from the clinical register, and double-checked by the researcher and patient during the visit.

In this survey, the following will be noted: 1. Demographic data: age, gender, civil status, place of origin, level of studies, social class (according to the categories proposed by the Spanish Epidemiology Society). 2. Medication: long-term medication, acute medication (taken in the last 30 days). 3. Chronic health conditions related to higher risk of RTI (Table 3). 4. Alcohol consumption (measured using the AUDIT-C test). 5. Consumption of psychoactive substances (cocaine, ecstasy and others) during the last year, as self-reported by the patient and self-declared dependency level of psychoactive substances in the last month. 6. Estimated level of perception risk, as assessed by the health professional, and rated using a scale from 0 (no risk) to 10 (maximum risk). 7. Driving data: type of driver's license, length of time driver's license held; type of vehicle most usually driven (moped, motorbike, car, others); professional driver (y/n); time spent driving in hours per week; type of road usually used (urban, motorway or others); safety behaviours (use of seatbelts, use of helmet, use of car seats for children and adherence to speed limits). 8. Collision background in the last year (with or without injury); History of medical attention for traffic road injuries in the last year. 9. Self-declared self medicating. 10. Self evaluation of state of health (using the SF-12 test). 11. Self-perception of risk. Individuals will be asked to score their own risk for RTIs, when compared to subjects with their same gender and age, rated in a scale from 0 to 10.

-Telephone survey: In the telephone survey carried out annually by a trained interviewer the following data will be collected and reviewed: 1. Collisions in the last year: date, time of day and day of the week when it occurred; type of road where the collision occurred; vehicle being driven and other vehicles implicated in the crash; medical attention needed (Yes/No/type); need for a sick leave due to traffic injuries (Yes/No/duration); after-effects (Yes/No/type); approximate material costs/vehicle repairs needed (Yes/No/Costs). 2. Newly diagnosed long-term conditions (in the last year). 3. Chronic and acute medication recently taken (time taken and coded according to therapeutic risk group). 4. Self-reported consumption of psychoactive substances. 5. Changes in driving conditions: type of vehicle usually driven, time spent driving in hours per week; type of road usually used (urban, motorway or others); safety behaviour (use of seatbelts, use of helmet, use of car seats for children and adherence to speed limits). 6. Changes in level of self-perception of risk (as reported by the subject of study).

### Statistical analysis

The characteristics of the population will be outlined using a descriptive univariant analysis, calculating the average, standard deviation, median, minimum and maximum values for continuous variables, and frequency and percentages for categorical variables.

The results of the descriptive part will be expressed with their confidence interval (CI 95%). In order to investigate the distribution of the risk factors associated with suffering an RTI according to age and gender, bivariant comparisons will be carried out using the Chi-square test between categorical variables and the Student's t-test between continuous and categorical variables. In order to analyse the association between the risk perception of an RTI (low/medium/high) and the different risk factors considered, an unconditional binary logistical regression model will be implemented. For the risk perception considered as an ordinal scale, a multiple lineal regression will be implemented. For the selection of the variables for the multivariate model, the methodology proposed by Hosmer-Memeshow [57], Cobo [58] and Greenland [59] will be implemented. In the initial multivariate model, the significant bivariate level variables will be introduced, based on the level of significance p = 0.25 and the variables considered to be clinically relevant. Confusion, interaction and co-linearity factors will be analysed. The adjustment of the model will be evaluated using the Hosmer-Lemeshow test and the area under the curve.

All statistical tests will be carried out with a confidence level of 95% and supposing a bilateral contrast. The analyses with be carried out using the statistics package SPSS.

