## Objectives

Main aim: to assess the distribution of the risk factors associated with RTI in a driving population assigned to a group of participating primary health care centres in the city of Barcelona.

Secondary objectives: 1. To study the distribution of RTI risk factors relative to medications, illnesses, alcohol intake and/or consumption of psychoactive substances in the driving population in different groups according to age and gender. 2. To outline the correlation between the number of risk factors related to suffering an RTI and the background of registered collisions, having or not having recieved medical attention. 3. To assess the existing relationship between the self perception level of risk of RTI and the presence of chronic health conditions, medication or consumption of psychoactive substances.

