### Sample size calculation

The calculation was carried out using the population of men and women with a driving license in the Barcelona province from the age 16 and over, according to the 2005 census of drivers made available by the General Traffic Department (DGT). For sample calculation purposes, four age groups proportional to women and men were created. Accepting an alpha risk of 0.05 with a precision of +/- 0.05 percentage units in a bilateral contrast for an estimated proportion of 0.5, a random population sample of 385 subjects was determined for each age group. The total sample size is 1540 subjects (Table 3).

**Table 3 T3:** Sample size according to the estimated distribution in age and gender groups

	16-24 yrs	25-34 yrs	35-64 yrs	Above 74 yrs	Total
Men	214	212	228	317	971
Women	171	173	157	68	569

Total	385	385	385	385	1540

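### Equal age quotas with plain percentages: pooled all-ages estimates for the main aim are equal-weight averages of four age groups, hence biased for age-dependent factors

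*Protocol article*

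**What the plan says.** The main aim (Protocol article, Objectives) is "to assess the distribution of the risk factors associated with RTI in a driving population" attached to the participating centres. Results by age and gender are a secondary objective.

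Under Sample size calculation, "a random population sample of 385 subjects was determined for each age group", and "The total sample size is 1540 subjects". Every age column of Table 3 totals 385. The 2005 driver census enters through the split by sex within each age group ("four age groups proportional to women and men were created"), not through the size of the groups.

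Recruitment Process gives a second allocation: each collaborating researcher enrols 16 subjects, two in each age-by-sex cell. This again makes the age groups equal, but it also makes the sexes equal.

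Statistical analysis describes the population by "calculating the average, standard deviation, median, minimum and maximum values for continuous variables, and frequency and percentages for categorical variables". Descriptive results carry 95% confidence intervals. No weight, standardisation or stratified variance is named. The limitations section restricts generalisation to urban populations and does not mention the quotas.

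**The concern.** The allocation is disproportionate by design. That suits estimates within an age group, which is what the precision calculation targets. For a statement about drivers of all ages, the age groups have to be recombined in their population proportions, and the analysis text does not say this will be done. A plain pooled percentage counts a driver band of 30 years (35-64) the same as one of 9 years (16-24).

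The article itself treats age as relevant: its Background reports injury figures that differ by age and remarks that long-term conditions and age tend to occur together. If a risk factor varies with age, the pooled figure generally estimates something other than the prevalence among drivers, and its interval is centred on that other quantity. A larger sample would not remove the error.

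**Working it through.** **1. The plan's own figure.** Inputs from Sample size calculation: "Accepting an alpha risk of 0.05", "in a bilateral contrast for an estimated proportion of 0.5", "with a precision of +/- 0.05 percentage units" (read as 5 percentage points). n = 1.96² × 0.5 × 0.5 / 0.05² = 384.15, rounded up to 385; 4 × 385 = 1540. Both figures reproduce. Table 3 adds up: 971 men + 569 women = 1540.

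**2. What the pooled percentage estimates.** With equal group sizes it is (p1 + p2 + p3 + p4)/4. The driver prevalence is W1p1 + W2p2 + W3p3 + W4p4, where W is each group's share of drivers. In general the two agree only if all shares are 25% or the prevalence is flat across age; otherwise agreement is by cancellation.

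**3. Illustrative size.** The document gives neither shares nor prevalences by age, so both are assumed. Share ranges: 16-24, 8-12%; 25-34, 22-25%; 35-64, 55-58%; oldest, 5-13%. Two extreme sets within them are S1 = 12/25/58/5% and S2 = 8/22/57/13%. As a contrast, shares proportional to band width are 9:10:30:10, with 10 years assumed for the oldest group.

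| Assumed prevalence by age (%) | Plain pooled | S1 | S2 | Band width |
|---|---|---|---|---|
| 2/3/10/40 (rising) | 13.75 | 8.79 | 11.72 | 12.68 |
| 20/15/8/2 (falling) | 11.25 | 10.89 | 9.72 | 10.00 |
| 5/10/25/60 (rising) | 25.00 | 20.60 | 24.65 | 25.34 |

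Example, first row: plain (2 + 3 + 10 + 40)/4 = 13.75; S1 0.12×2 + 0.25×3 + 0.58×10 + 0.05×40 = 8.79.

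Bias (plain minus weighted), in points for S1, S2 and band width:
- first row: +5.0, +2.0, +1.1
- second row: +0.4, +1.5, +1.3
- third row: +4.4, +0.4, -0.3

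The naive half-width is 1.96 × √(p(1-p)/1540): 1.7 points at 13.75%, 1.6 at 11.25%, 2.2 at 25%, and at most 2.5 (at 50%). The bias can therefore be well below the half-width or up to nearly three times it (5.0/1.7), and its sign can change.

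**4. Cost of weighting.** With equal group sizes the design effect is 4 × ΣW². S1: 4 × (0.0144 + 0.0625 + 0.3364 + 0.0025) = 1.66. The lowest value in the assumed ranges is about 1.51 (for example 12/22/55/11%). Effective sample size is 1540/1.66 to 1540/1.51, about 930 to 1020. The half-width at 50% is 1.96 × √(0.25 × design effect / 1540), or 3.1 to 3.2 points. Clustering by centre is not included.

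**5. Sex allocation.** Table 3 has 68/385 = 17.7% women in the oldest group and 569/1540 = 36.9% overall; the recruitment quota implies 50% in both. As an illustration, take the Table 1 general-population rates for hypnotics (4.02% men, 10.62% women). In the oldest group the Table 3 split gives (317×4.02 + 68×10.62)/385 = 5.2%, and a 50:50 split gives 7.3%. Over the whole sample the figures are (971×4.02 + 569×10.62)/1540 = 6.5% and 7.3%. Estimates that pool the sexes thus depend on which allocation is followed, even within an age group.

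**The case against.** The strongest reply is that the analysis section never says the percentages are unweighted, and that a condensed article may leave weighting to a fuller document. That is fair as to intent. But the article does fix the allocation, the target and the summary statistics, and taken together these do not estimate the target. Someone following the text would produce unweighted figures.

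Several limits stand in full:
- Precision was set per age group, and comparisons by age and gender are planned. Age-specific estimates are not biased by the age allocation.
- The regressions estimate associations, for which sampling weights are not automatically needed. The point does not extend to them.
- Every share and prevalence used above is assumed.

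A reader might infer that the headline result is wrong for nearly every risk factor, or that the youngest and oldest are known to be over-represented by a given amount. The document does not support either. It gives no age shares, and its drug-use table is split by sex only. Over-representation at the extremes is a reasonable inference from the band widths, not a stated figure, and under band-width shares one rising pattern shows almost no bias.

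A further reply is that weighting to the driver census would not make this a probability sample. That also stands: although the abstract calls the sample randomly selected, subjects are consecutive attenders at centres that volunteered.

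**Conclusion.** The point holds for pooled all-ages estimates, which are what the main aim calls for. As written, they are equal-weight averages over four age groups and will generally be biased for factors whose prevalence varies with age. The mismatch follows from the text alone. Its size does not: under the assumed shares and prevalences the bias lies between under 1 point and about 5 points, against a naive half-width of at most 2.5, and the direction is not determined. Factors that are flat across age are unaffected.

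The conflict between the recruitment quota and Table 3 adds a separate dependence on sex, which reaches any estimate that pools men and women. The per-group and total sample sizes are correct for their stated purpose.

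**What to change.** 1. **State one target population.** The area is given as the province (abstract, Sample size calculation), the city (Objectives), and the province with the metropolitan area (after the exclusion criteria), while Study population means drivers attended at the participating centres. Reconcile the Table 3 age bands, which pass from 35-64 to over 74: unless this is a misprint, no weight can recover ages 65-74. Reconcile the sex split in Table 3 with the quota in Recruitment Process.
2. **Say how all-ages figures are formed.** Weight or directly standardise every all-ages estimate to the age-by-sex distribution of that population, for example the driver census already used for Table 3, taken for the matching area. Use design-based confidence intervals that also allow for clustering by centre, for instance with a complex-survey procedure and not a plain case weight. Alternatively, limit headline results to age- and sex-specific estimates.
3. **Add to the limitations** that weighting corrects only the quota imbalance, not the selection of consecutive attenders at volunteer centres.

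Cost: a paragraph of text and a weight variable, since age and gender are already collected. N is unchanged. Under the assumed shares the overall half-width rises from about 2.5 to 3.1-3.2 points before clustering, still inside the planned 5.

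### Under the Table 3 allocation, the planned unadjusted comparison of risk factors between men and women is confounded by age; it should be stratified by age group

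*Protocol article*

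**What the plan says.** Secondary objective 1 concerns risk factors (medication, illness, alcohol, psychoactive substances) "in the driving population in different groups according to age and gender" (protocol article, Objectives). For this the Statistical analysis section states that "bivariant comparisons will be carried out using the Chi-square test between categorical variables", and that Student's t-test is used where one variable is continuous. It mentions no stratification or adjustment. The multivariable models, with their check for confounding and interaction, are specified for risk perception only. The tests are formal: "All statistical tests will be carried out with a confidence level of 95% and supposing a bilateral contrast".

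The Sample size calculation section says that "four age groups proportional to women and men were created" and that "a random population sample of 385 subjects was determined for each age group". Table 3 then splits each 385 by sex. The row for men reads "Men 214 212 228 317 971"; the row for women is 171, 173, 157, 68, total 569.

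The Recruitment Process section describes a different quota. Each researcher enrols 16 people, two in each of the eight age-by-gender cells. The same section also has each centre recruit to a required age and sex distribution, without giving numbers.

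**The concern.** Table 3 gives the two sexes very different age mixes. Men in this sample are older than women because every age group is set to 385 and the oldest is mostly male. A test that pools over age attributes to gender whatever part of a risk factor follows age.

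If chronic conditions and medication rise with age, men can appear sicker than women of the same age are. If recreational drug use falls with age, women can appear to be heavier users. Where a risk factor rises with age and is truly more common in women, the two effects work against each other and the difference shrinks. The pooled contrast is not the sex difference among drivers either, because the age groups are not sampled in proportion to their size in the driving population. A reader of the results would probably take it for one of the two.

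**Working it through.** **The plan's own figure.** From "Accepting an alpha risk of 0.05 with a precision of +/- 0.05 percentage units in a bilateral contrast for an estimated proportion of 0.5": n = 1.96² × 0.5 × 0.5 / 0.05² = 384.15, rounded up to 385; 4 × 385 = 1540. This agrees with the stated total, and the rows and columns of Table 3 add up.

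**Age mix by sex (Table 3, youngest to oldest).**
- Men: 214, 212, 228, 317 of 971 = 22.0%, 21.8%, 23.5%, 32.6%.
- Women: 171, 173, 157, 68 of 569 = 30.1%, 30.4%, 27.6%, 12.0%.
- Association of age group with sex: chi-square 83.7 on 3 df.

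**Pooled prevalence when men and women of the same age are identical.** Pooled prevalence = sum of (cell size × age-specific prevalence) / number of that sex. The documents give no risk-factor prevalences by age, so the gradients are assumptions. For 5/8/25/70%:
- Men: (10.7 + 16.96 + 57 + 221.9) / 971 = 306.56 / 971 = 31.6%.
- Women: (8.55 + 13.84 + 39.25 + 47.6) / 569 = 109.24 / 569 = 19.2%.
- Difference: 12.4 points, with no gender effect at any age.

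**Rejection rates.** Binomial counts were simulated in each age-by-sex cell, with no gender effect within age and two-sided 5% tests. The crude test is Pearson chi-square by sex; the stratified test is Mantel-Haenszel over the four age groups. The last column applies the crude test to equal cells of 193 (1540 / 8 = 192.5).

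| Assumed prevalence, youngest to oldest | Pooled men vs women, Table 3 | Crude, Table 3 | Stratified, Table 3 | Crude, equal cells |
|---|---|---|---|---|
| 20% throughout | 20.0% vs 20.0% | 5% | 5% | 5% |
| 10/11/12/16% | 12.6% vs 11.6% | 9% | 5% | 5% |
| 10/12/15/25% | 16.5% vs 13.8% | about 30% | 5% | 5% |
| 20/12/5/1% | 8.5% vs 11.2% | about 39% | 5% | 4% |
| 5/8/15/40% | 19.4% vs 12.9% | 93% | 5% | 3% |
| 5/8/25/70% | 31.6% vs 19.2% | 100% | 5% | 1.5% |

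**Dilution of a real excess in women.** Assume male prevalence of 2/4/8/15% and the same ratio of women to men at every age.
- Ratio 1.5: pooled men 78.55 / 971 = 8.1%, women 49.65 / 569 = 8.7%, so the ratio shrinks to about 1.08. Power is 7% crude and 62% stratified.
- Ratio 2: power is about 64% crude and 99% stratified.
- Ratios from Table 1: anxiolytics 12.38 / 5.72 = 2.16, antidepressants 9.77 / 3.73 = 2.62, hypnotics 10.62 / 4.02 = 2.64. Crude power is about 82%, 99% and 99%.

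**Sex difference among drivers.** This uses the steepest gradient (5/8/25/70%), Table 3's sex split within each age group and assumed driver age shares. Shares of 10/25/60/5% give 22.3% vs 19.1% (3.1 points). Shares of 8/22/65/5% give 23.1% vs 20.1% (3.0 points). Shares of 12/25/53/10% give 25.1% vs 19.5% (5.5 points). The sample contrast is 12.4 points.

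**The case against.** The strongest reply is that the defect is conditional. Followed literally, the two-per-cell quota in the Recruitment Process section gives both sexes the same age mix, and the crude test then shows no inflation (1.5-5%). This stands. The article does not settle which quota governs, and an analysis that is sound under only one of two conflicting quotas is badly fixed.

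Second, pooling over age is inferred. The objective is descriptive, precision is set per age group, and the Difficulties and limitations section disclaims causal assessment. Results by gender within age group may therefore be intended. But the named method is an unadjusted bivariate test, the same section specifies adjustment for another outcome only, and the tests are two-sided at 5%. Disclaiming causality does not make the pooled contrast describe the driving population.

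Four stronger readings are tempting and are not supported:
- **That the test responds to the age mix and not to gender.** Inflation depends on age gradients the documents do not give; it is absent for a flat factor, and the test still responds to true gender differences.
- **That the plan would hide the excess of anxiolytics, antidepressants and hypnotics in women.** At the Table 1 ratios the difference is diluted but mostly still detected.
- **That the quota alone creates the difference.** Table 3's sex split comes from the driver census and older drivers are mostly men, so part of the pooled contrast is real (about 3-5.5 of 12.4 points in the steepest scenario).
- **That the chi-square test is invalid.** It is valid for equal pooled prevalence in the recruited sample; the trouble is that this hypothesis mixes age with gender.

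**Conclusion.** The concern holds in a conditional form. If Table 3 is followed, the stated gender comparison is confounded by age for any age-related risk factor. It can reject through age mix alone and can weaken a true excess in women, to the extent shown above. In the steepest scenario it also overstates the sex difference among drivers by a factor of about two to four (12.4 / 5.5 = 2.3; 12.4 / 3.0 = 4.1).

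The age imbalance itself is certain, because it follows from Table 3. The rejection rates and power rest on assumed age gradients, and the comparison with drivers also rests on assumed age shares. Because this is a secondary, descriptive objective and the remedy is nearly free, the change should be made, but it does not threaten the study.

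**What to change.** In the Statistical analysis section, make the gender comparison age-stratified:
- Categorical risk factors: Cochran-Mantel-Haenszel test and common odds ratio over the four age groups.
- Continuous risk factors: a linear model with gender and age group.
- Show prevalence by gender within each age group.
- If one male and one female figure are also reported, standardise both to the age distribution of the driver census used for the sample size.

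Separately, reconcile Table 3 with the two-per-cell quota in the Recruitment Process section and state which one governs. The stratified analysis is valid under either.

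The cost is a change of wording and one extra stratified table per risk factor. Age and gender are already collected, and the planned package, SPSS, has these methods.

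### The named Student's t-test for sex comparisons of continuous variables drifts moderately from its 5% level if recruitment follows Table 3 and spread differs by sex; naming Welch's test would avoid this at almost no cost

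*Protocol article*

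**What the plan says.** The Statistical analysis section introduces the tests with the words "In order to investigate the distribution of the risk factors associated with suffering an RTI according to age and gender, bivariant comparisons will be carried" and assigns the chi-square test to pairs of categorical variables and "the Student's t-test between continuous and categorical variables". It adds: "All statistical tests will be carried out with a confidence level of 95% and supposing a bilateral contrast". The analyses are to be "carried out using the statistics package SPSS". Neither a pooled nor an unequal-variance version is specified, and no check of variances is mentioned.

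Group sizes come from two places that disagree:

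- The Sample size calculation section says that "four age groups proportional to women and men were created". Table 3 then gives 971 men and 569 women, with 317 men and 68 women in the oldest column.
- Under Recruitment Process, each researcher enrols two people per age-and-sex cell, which is 1:1 by sex. The same paragraph also tells centres to respect the required age and sex distribution.

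No standard deviation by sex is given for any variable.

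**The concern.** Student's test, taken at its name, pools the two variances. It keeps its level under unequal variances only when the groups are of about equal size. If the larger group varies more, the pooled standard error is too large: the test is conservative and its interval too wide. If the smaller group varies more, the test rejects too often and the interval is too narrow.

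Table 3 plans unequal numbers of men and women, so a sex comparison of a continuous variable could be distorted in either direction. At stake are secondary descriptive comparisons by sex. The AUDIT-C score, if analysed as a score, is the clearest example because alcohol intake is named in secondary objective 1.

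**Working it through.** **The plan's own figures.** The Sample size calculation section reads: "Accepting an alpha risk of 0.05 with a precision of +/- 0.05 percentage units in a bilateral contrast for an estimated proportion of 0.5". Taking the precision as 0.05 on the proportion scale, n = 1.96² × 0.5 × 0.5 / 0.05² = 384.15, rounded up to 385 per age group; 4 × 385 = 1540. Both stated figures reproduce. Table 3 adds up: 971 + 569 = 1540, and each column sums to 385.

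**Inputs.** Group sizes are from Table 3. The SD ratio between the sexes is an assumption, because the article gives none: 1.25 to 1.5, in either direction.

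**Formula.** With sizes n₁ (men) and n₂ (women) and standard deviations s₁ and s₂:

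- expected pooled squared standard error: P = [(n₁−1)s₁² + (n₂−1)s₂²]/(n₁+n₂−2) × (1/n₁ + 1/n₂)
- true squared standard error: T = s₁²/n₁ + s₂²/n₂
- k = √(P/T); true two-sided size ≈ 2[1 − Φ(1.96k)]

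**Worked case, 971 v 569, men's SD 1.5 times women's.** Pooled variance = (970 × 2.25 + 568)/1538 = 1.788. P = 1.788 × (1/971 + 1/569) = 0.004985. T = 2.25/971 + 1/569 = 0.004075. k = √(0.004985/0.004075) = 1.106. Size = 2[1 − Φ(2.168)] = 3.0%.

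**All settings.** The last column is the size of the pooled test in 100,000 simulated normal data sets per setting.

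| Groups | Larger SD | Ratio | k | Size, formula | Size, simulated |
|---|---|---|---|---|---|
| 971 v 569 | men | 1.25 | 1.059 | 3.8% | 3.8–3.9% |
| 971 v 569 | men | 1.5 | 1.106 | 3.0% | 3.0–3.1% |
| 971 v 569 | women | 1.25 | 0.944 | 6.4% | 6.4–6.5% |
| 971 v 569 | women | 1.5 | 0.904 | 7.6% | 7.5% |
| 317 v 68 | men | 1.25 | 1.154 | 2.4% | 2.4% |
| 317 v 68 | men | 1.5 | 1.290 | 1.1% | 1.2% |
| 317 v 68 | women | 1.25 | 0.866 | 8.9% | 8.9–9.0% |
| 317 v 68 | women | 1.5 | 0.775 | 12.9% | 12.9% |

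**Younger bands.** Simulated size across ratios up to 1.5 in either direction is 4.2–6.0% for 214 v 171, 4.2–5.9% for 212 v 173 and 3.5–6.8% for 228 v 157.

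**Intervals.** Overall, coverage of the nominal 95% interval is 100% minus the size: about 96–97% if men vary more and 92.5–93.6% if women do.

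**Power.** With men's SD 1.5 times women's and a difference for which Welch has about 80% power, the pooled test has 74% overall and 61% at 317 v 68.

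**Welch.** Its simulated size stays at 4.9–5.1% throughout. With equal variances the two tests have nearly the same power: 80.0% pooled v 79.9% Welch at 971 v 569, and 80.0% v 79.4% at 317 v 68.

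**Equal groups.** If n₁ = n₂ = n, then P = [(s₁² + s₂²)/2] × (2/n) = (s₁² + s₂²)/n = T, so k = 1 for any SD ratio. The 1:1 quota would remove the distortion.

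**The case against.** The case for leaving the text alone has real weight.

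- **The variance option is not spelled out.** One line in a condensed article names a family of tests, and the detail may sit in an analysis plan. That is fair, but the article does name a test, and by that name it is the pooled one. Software that offers both versions would not settle which is reported.
- **The imbalance is not certain.** The 1:1 quota contradicts Table 3, and under 1:1 nothing goes wrong. This stands as a condition on the point. It does not favour the pooled test, since Welch holds its level under either reading.
- **Unequal spread is assumed.** This also stands; the direction is unknown too. One indication that it is not far-fetched: Table 3 puts 317/971 = 33% of men but 68/569 = 12% of women in the oldest band. With uniform ages within the bands and a mean of 78–85 years in the top band, the SD of age would be 1.23–1.27 times larger in men. That concerns age and, plausibly, variables tied to it; it says nothing about AUDIT-C.
- **The scope is narrow.** Secondary objective 1 lists medication, illness, alcohol and psychoactive substances, mostly categorical and so tested by chi-square. Self-perceived risk belongs to objective 3 and goes to regression. Of the scores collected, only AUDIT-C clearly falls under objective 1, and the article does not say whether it is analysed as a score.

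A reader might infer from 317 v 68 that the planned sex comparisons have error rates anywhere from 1% to 13%. The document does not support that: it plans comparisons by age and gender but never explicitly a sex test within each age band. Nor are the groups very unequal overall, at 1.7:1.

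**Conclusion.** The point holds as a minor improvement. It rests on three conditions together: Student's test means the pooled test, recruitment follows Table 3, and spread differs by sex. Under an assumed SD ratio of 1.25 to 1.5, the overall sex comparison then has a true size of about 3.0–3.9% or 6.4–7.5% in place of 5%, depending on which sex varies more. If any one condition fails, there is no distortion. The larger figures for the oldest band apply only if that within-band test is actually run. The main aim, a descriptive distribution of risk factors, is not affected.

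**What to change.** In the Statistical analysis section, replace Student's t-test by Welch's unequal-variance t-test, reported with its confidence interval, for every two-group comparison of a continuous variable. Do not choose between the two by a preliminary variance test. The cost is a few words and a negligible loss of power if variances are in fact equal (0.1 percentage points at 971 v 569 and 0.6 at 317 v 68 in the simulations above).

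Separately, reconcile the sex distribution in Table 3 with the quota under Recruitment Process. The change to Welch need not wait for that.
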